### Randomization, Allocation, and Blinding

Using a 1:1 allocation, participants will be randomized into either the intervention or control group using a computer-generated stratified block randomization with blocks varying between 4 to 8 via REDCap (Research Electronic Data Capture; Vanderbilt University). Stratification based on the site of recruitment will be implemented. Due to the nature of ECEM-TZ, blinding will not be possible for mothers (ie, mothers will know if they receive text messages or not). To minimize bias at the participant level, all mothers will receive the same in-hospital care. Due to the nature of the intervention, mothers in the control group will not be exposed to the intervention text messages. Hospital staff (nurse midwives, physicians, and other health care providers) will be blind to participant group allocation to ensure both groups receive the standard discharge education. The researchers will be aware of participant allocation but will not be involved in data collection from participants or the randomization process. The research assistants will be blinded to allocation at baseline (T1) but not at T2.

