### Outcome Measures

Baseline data will be collected in person in the hospital while follow-up data at 6 weeks post partum will be collected by telephone. Research assistants will attempt to contact participants until 10 weeks post partum to obtain complete follow-up data. Table 1 shows the outcome assessment time points.

**Table 1 table1:** Outcome assessment time points.

Outcome	Baseline (T1^a^)	6-Week follow-up (T2)
Eligibility screen	✓	
Informed consent	✓	
Randomization	✓	
Demographics	✓	
Newborn care knowledge	✓	✓
Parenting self-efficacy	✓	✓
Breastfeeding self-efficacy	✓	✓
Postpartum anxiety	✓	✓
Postpartum depression	✓	✓
Neonatal morbidity and mortality		✓
Postnatal clinic attendance		✓
Implementation quality—evaluation survey		✓
Implementation extent	✓	✓

^a^T: time point.

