### Effectiveness Outcomes

To measure the effectiveness of ECEM-TZ, the following will be assessed:

Newborn care knowledge: Knowledge will be assessed using a modified questionnaire developed by McConnell and colleagues [22] assessing newborn care knowledge. The questions determine whether mothers can identify danger signs, handwashing practices, cord care, newborn thermal care, and breastfeeding. A total sum of the number of items mothers can identify will be created. Additionally, binary variables will be created to determine whether mothers can identify three or more newborn danger signs, two or more best practice hand washing, two or more cord care practices, three or more thermal care practices, and two or more breastfeeding practices. Based on these variables, a summative score will be created ranging from 0 to 5, with a higher score representing increased newborn care knowledge.Maternal self-efficacy: Parenting self-efficacy will be measured using the Karitane Parenting Confidence Scale [20]. This 15-item scale was developed to assess the perceived self-efficacy of mothers of newborns from birth to aged twelve months and has acceptable internal consistency (Cronbach α=0.81) and test-retest reliability (*r*=0.88) [20]. A cutoff score of 39 or less (out of a possible 45) was determined to be a clinically low perceived parenting self-efficacy [20]. The Kiswahili version was piloted as part of the development phase.Breastfeeding self-efficacy: Breastfeeding self-efficacy will be measured using the Breastfeeding Self-Efficacy Scale—Short Form [23]. This 14-item tool was developed originally in Canada and has been translated into Kiswahili and determined to be valid and reliable [24]. Higher scores indicate higher breastfeeding self-efficacy.Postpartum depression: Depression will be measured using the Edinburgh Postnatal Depression Scale (EPDS) [25]. The EPDS is a self-report screening scale with 10 items that can indicate if a respondent has symptoms related to perinatal depression [25,26]. The EPDS is valid for assessing depressive symptoms across the perinatal period with a score >12 considered as high symptoms of depression. The EPDS has been used in a variety of African countries to measure perinatal depression [27-29]. The EPDS has already been translated into Kiswahili and has been modified for contextual differences [30].Postpartum anxiety: Anxiety will be measured using the Generalized Anxiety Disorder (GAD)-7 [31], which is a 7-item scale used to assess GAD. The scale ranges between 0 and 21, with scores of 10 or greater indicative of generalized anxiety at a moderate or severe level. The GAD-7 has already been translated into Kiswahili [32] and has been widely used to measure perinatal anxiety in African countries, including in Tanzania [33,34].Newborn morbidity and mortality: The 6-week follow-up survey will collect information on morbidity (eg, diarrhea, jaundice, or infection), need for readmission due to illness, and mortality.Postnatal clinic attendance at six weeks: The 6-week follow-up survey will collect information on the number and date of postnatal contacts.

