
### Implementation Outcomes

To measure the implementation of ECEM-TZ, 3 measurement tools will be used.

Data related to recruitment will be collected, such as the number of women approached at each site and the number of women randomized.Output data available through the Twilio and TextIt platforms will be collected per participant, including the number of messages sent, messages delivered, error messages, opt-out rates, and response rates.At the final follow-up at 6 weeks post partum, mothers in the intervention group will evaluate the program and be asked about the number of messages they recall receiving, user experience, perspectives on the frequency and timing of messages, and what they liked and did not like about ECEM-TZ.

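### The research assistants who make the 6-week calls know the allocation, with no reason given, so outcomes that depend on the interviewer, chiefly newborn care knowledge, are open to avoidable assessor bias

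*Protocol article*

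**What the plan says.** The section on randomization, allocation and blinding sets out who knows the arm:

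- Mothers: "blinding will not be possible for mothers", because they either receive messages or do not.
- Hospital staff are blinded.
- Researchers: "The researchers will be aware of participant allocation but will not be involved in data collection from participants or the randomization process".
- Assistants: "The research assistants will be blinded to allocation at baseline (T1) but not at T2".

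Under Outcome Measures, "follow-up data at 6 weeks post partum will be collected by telephone", and "Research assistants will attempt to contact participants until 10 weeks post partum to obtain complete follow-up data". Ethical Considerations has a research assistant entering the data into REDCap.

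For knowledge, the Effectiveness Outcomes section says "A total sum of the number of items mothers can identify will be created". Threshold variables for five domains are then derived and added into a 0 to 5 score. The section does not say who codes the answers. Depression, anxiety, both self-efficacy measures, newborn morbidity and mortality, and clinic attendance are also measured at T2.

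One T2 element differs by arm. Under Implementation Outcomes, "mothers in the intervention group will evaluate the program and be asked about the number of messages they recall receiving". Its place in the call is not stated.

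**The concern.** Assessor blinding is in place where it matters least and dropped where it matters most. The Procedure section puts the baseline questionnaire before randomization, so at T1 there is no allocation to know. At T2, where every effectiveness outcome is measured, the caller knows it.

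Nothing in the article forces this. Randomization runs in REDCap, messages go out through an automated platform, and follow-up is by telephone. The one arm-specific element, the program evaluation, could come after the outcome forms.

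At stake is the knowledge outcome. How far a caller prompts, and how a loosely worded answer is recorded, leave room for judgement. The sample size section uses the proportion of mothers with a full score, so for a mother one item short in exactly one domain, a single generous credit turns failure into success. The four limitations listed under Strengths and Limitations do not include unblinded outcome assessment.

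**Working it through.** **1. The plan's own figure.** Inputs from the Sample Size section: 90% against 70%, 80% power, two-sided α of 0.05. With the pooled-variance formula and no continuity correction:

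n per arm = [1.960 × √(2 × 0.80 × 0.20) + 0.842 × √(0.90 × 0.10 + 0.70 × 0.30)]² / (0.20)² = (1.109 + 0.461)² / 0.04 = 61.6, rounded up to 62, or 124 in total.

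This matches the article. The point about blinding does not change it.

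**2. Which outcomes are exposed.**

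| T2 outcome | Room for interviewer influence |
|---|---|
| Newborn care knowledge | Greatest: prompting, and what counts as an item identified |
| Depression, anxiety, self-efficacy scales | Some: fixed items answered by the mother, but by telephone |
| Reported newborn morbidity | Some: depends on how illness is asked about and recorded |
| Number and date of clinic contacts | Little |
| Newborn mortality | Little |

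**3. Illustration of size.** The documents give no estimate of assessor bias, so the lift is an assumption and a range is shown.

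- Arms: 72 intervention and 71 control (Results), all followed up.
- True full-score rate: 70% in both arms (the article's control assumption), so there is no real effect.
- Bias: the recorded intervention rate is raised by a fixed number of points, with no over-crediting in controls.
- Test: Wald test of the log odds ratio from logistic regression, two-sided 5%. Its rejection probability is the sum of the two binomial probabilities over all outcome pairs with |z| > 1.96.

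A lift of L points means that a share L/30 of the intervention mothers who truly fall short is recorded as successful. The expected number of such mothers is 72 × L/100.

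| Lift (points) | Share of true failures converted | Mothers converted | Rejection rate, 72/71 | Rejection rate, 62/62 |
|---|---|---|---|---|
| 0 | 0% | 0 | 4.9% | 4.6% |
| 2 | 6.7% | 1.4 | 5.6% | 5.3% |
| 3 | 10.0% | 2.2 | 6.6% | 6.1% |
| 5 | 16.7% | 3.6 | 9.8% | 9.0% |
| 7 | 23.3% | 5.0 | 15.1% | 13.6% |
| 10 | 33.3% | 7.2 | 27.2% | 24.2% |

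The last column shows the planned 62 per arm.

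**4. A continuous score.** The plan also analyzes total and summative scores by analysis of covariance. As a normal approximation that ignores the baseline adjustment, a spurious shift of s standard deviations with 71 per arm gives k = s × √(71/2). The rejection rate is Φ(k − 1.96) + Φ(−k − 1.96). For s = 0.1, 0.2 and 0.3 this is 9.2%, 22.2% and 43.2%. Again, s is assumed.

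**The case against.** The article discloses this choice openly and nowhere contradicts it. It keeps the researchers who know the allocation out of data collection and blinds hospital staff. That is true, but disclosure does not remove the bias, and the article neither justifies the choice nor lists it as a limitation.

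Several stronger readings are tempting, and the documents do not support them:

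- **That the assistants score every outcome.** The article says they make the contacts and that one of them enters the data. Whether knowledge answers are credited during the call or coded later, and by whom, is not stated.
- **That all T2 outcomes are equally at risk.** Deaths and dated contacts leave little discretion. The depression measure is described thus: "The EPDS is a self-report screening scale with 10 items". The other scales also have fixed items.
- **That hiding the arm and moving one survey would be enough.** Mothers know their arm and may reveal it while talking about topics the messages cover. Nor does the article say who sees the randomization result or registers telephone numbers. Blinded callers would also leave untouched any reporting bias from unblinded mothers.
- **That callers tried harder to reach one arm.** The 10-week limit is the same for everyone, and nothing documents different effort.

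On size, a 10-point lift means miscrediting a third of the intervention arm's true failures, and small lifts do little harm. That objection stands, which is why the table begins at 2 points.

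**Conclusion.** The concern holds in limited form. The article expressly leaves the T2 callers unblinded without giving a reason, so a removable source of bias remains in the outcomes that depend on the interviewer. Knowledge is the most exposed and is the outcome on which the trial is powered.

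The inflation of false-positive risk runs from negligible (5.6% for a 2-point lift) to serious (27.2% for 10 points). These figures rest on an assumed one-sided lift, a true 70% in both arms and complete follow-up of 72 and 71. They show sensitivity; they are not evidence that bias occurred. This is a design weakness that should be addressed, not an error that invalidates the trial.

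**What to change.** T2 calls ended on September 21, 2024, and the legend to Figure 1 says that analysis was not complete. What can still be done:

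1. State in the limitations and the results paper that T2 outcomes were collected by interviewers who knew the allocation, and say who coded the knowledge answers and how.
2. Limit claims on the judgement-dependent outcomes accordingly, knowledge first.
3. If verbatim answers were kept, have existing staff recode the knowledge items with the arm hidden, and report the analysis on the recoded data.

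The first two cost a few sentences. The third costs staff time for at most 143 records and is possible only if the answers were recorded in full.

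For any repeat of the design:

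- Remove the T2 interviewers' access to the arm field in REDCap.
- Ask mothers at the start of the call not to mention messages.
- Complete and lock all effectiveness forms before branching logic opens the evaluation survey.
- Record any unmasking before the lock, and run a sensitivity analysis without those interviews.

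This takes user rights, form order and one line of script, with no extra staff and no change in sample size. The protection is partial: some mothers will still reveal their arm, and self-report bias from unblinded mothers remains.

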### Setting

This study is being conducted in Dar es Salaam, Tanzania, which is in East Africa. Participants will be recruited from the Mwananyamala Regional Hospital and Sinza Palestina Hospital. The Mwananyamala Regional Hospital is a large government-run hospital that has 70 to 90 deliveries per day. The Sinza Palestina Hospital is a governmental, public hospital that has up to 50 deliveries per day.

### Inclusion Criteria

Mothers are eligible if they meet the following criteria: (1) have given birth within the past 48 hours, (2) have daily access to a mobile phone with text messaging capabilities, (3) are aged older than 18 years, and (4) speak and read English or Swahili. Participants will be excluded if (1) newborns die or are expected to die before leaving the hospital; (2) they have no access to a mobile phone, either personal or shared; (3) they are unwilling to receive SMS messages; (4) decline to participate; (5) are experiencing major postnatal complications expected to impact learning or ability to consent while in the hospital (eg, postpartum hemorrhage or seizures); or (6) participated in ECEM-TZ development phase.

### Ethical Considerations

Ethics approval has been received from Dalhousie University (REB#2018-4538), Muhimbili University of Health and Allied Science (REB#MUHAS-REC-7-2019-010), and National Medical Institute of Research (REB#NIMR/HQ/R.8c/Vol.I/2457). All participants will be provided with written and verbal information and will complete a written consent form before enrollment in the study. To maintain confidentiality, all study data will be identified using a study number unique to each participant on all questionnaires and surveys. All data will be entered into REDCap by a research assistant in Tanzania with the first author having access to the data. REDCap is a secure web application for building and managing online surveys and databases [21]. All participants will receive the equivalent of honorarium (TZS 10,000; approximately US $4) in phone vouchers to their airtime provider of choice.

### Outcome Measures

Baseline data will be collected in person in the hospital while follow-up data at 6 weeks post partum will be collected by telephone. Research assistants will attempt to contact participants until 10 weeks post partum to obtain complete follow-up data. Table 1 shows the outcome assessment time points.

**Table 1 table1:** Outcome assessment time points.

Outcome	Baseline (T1^a^)	6-Week follow-up (T2)
Eligibility screen	✓	
Informed consent	✓	
Randomization	✓	
Demographics	✓	
Newborn care knowledge	✓	✓
Parenting self-efficacy	✓	✓
Breastfeeding self-efficacy	✓	✓
Postpartum anxiety	✓	✓
Postpartum depression	✓	✓
Neonatal morbidity and mortality		✓
Postnatal clinic attendance		✓
Implementation quality—evaluation survey		✓
Implementation extent	✓	✓

^a^T: time point.

### Effectiveness Outcomes

To measure the effectiveness of ECEM-TZ, the following will be assessed:

Newborn care knowledge: Knowledge will be assessed using a modified questionnaire developed by McConnell and colleagues [22] assessing newborn care knowledge. The questions determine whether mothers can identify danger signs, handwashing practices, cord care, newborn thermal care, and breastfeeding. A total sum of the number of items mothers can identify will be created. Additionally, binary variables will be created to determine whether mothers can identify three or more newborn danger signs, two or more best practice hand washing, two or more cord care practices, three or more thermal care practices, and two or more breastfeeding practices. Based on these variables, a summative score will be created ranging from 0 to 5, with a higher score representing increased newborn care knowledge.Maternal self-efficacy: Parenting self-efficacy will be measured using the Karitane Parenting Confidence Scale [20]. This 15-item scale was developed to assess the perceived self-efficacy of mothers of newborns from birth to aged twelve months and has acceptable internal consistency (Cronbach α=0.81) and test-retest reliability (*r*=0.88) [20]. A cutoff score of 39 or less (out of a possible 45) was determined to be a clinically low perceived parenting self-efficacy [20]. The Kiswahili version was piloted as part of the development phase.Breastfeeding self-efficacy: Breastfeeding self-efficacy will be measured using the Breastfeeding Self-Efficacy Scale—Short Form [23]. This 14-item tool was developed originally in Canada and has been translated into Kiswahili and determined to be valid and reliable [24]. Higher scores indicate higher breastfeeding self-efficacy.Postpartum depression: Depression will be measured using the Edinburgh Postnatal Depression Scale (EPDS) [25]. The EPDS is a self-report screening scale with 10 items that can indicate if a respondent has symptoms related to perinatal depression [25,26]. The EPDS is valid for assessing depressive symptoms across the perinatal period with a score >12 considered as high symptoms of depression. The EPDS has been used in a variety of African countries to measure perinatal depression [27-29]. The EPDS has already been translated into Kiswahili and has been modified for contextual differences [30].Postpartum anxiety: Anxiety will be measured using the Generalized Anxiety Disorder (GAD)-7 [31], which is a 7-item scale used to assess GAD. The scale ranges between 0 and 21, with scores of 10 or greater indicative of generalized anxiety at a moderate or severe level. The GAD-7 has already been translated into Kiswahili [32] and has been widely used to measure perinatal anxiety in African countries, including in Tanzania [33,34].Newborn morbidity and mortality: The 6-week follow-up survey will collect information on morbidity (eg, diarrhea, jaundice, or infection), need for readmission due to illness, and mortality.Postnatal clinic attendance at six weeks: The 6-week follow-up survey will collect information on the number and date of postnatal contacts.

### Implementation Outcomes

To measure the implementation of ECEM-TZ, 3 measurement tools will be used.

Data related to recruitment will be collected, such as the number of women approached at each site and the number of women randomized.Output data available through the Twilio and TextIt platforms will be collected per participant, including the number of messages sent, messages delivered, error messages, opt-out rates, and response rates.At the final follow-up at 6 weeks post partum, mothers in the intervention group will evaluate the program and be asked about the number of messages they recall receiving, user experience, perspectives on the frequency and timing of messages, and what they liked and did not like about ECEM-TZ.

### Sample Size

The sample size was calculated based on the outcome of newborn care knowledge. While previous studies on postnatal education knowledge are significantly varied and no studies to date have reported on maternal postnatal education knowledge in Tanzania, we considered a binary summative score of 100% as the goal at 6 weeks post partum. Using a power of 80%, α of .05 (2-tailed), and assuming 90% of the intervention group and 70% of the control group will score 100% at 6 weeks, a total sample size of 124 is required. This is in line with our implementation sample size approach: recruiting across two hospitals to determine the feasibility of recruitment at these sites. We will aim for approximately similar numbers of participants at each site, recruiting for six weeks. Assuming two research assistants are recruiting five days per week at each hospital and each research assistant can recruit a minimum of 2 participants per day, this would be approximately 20 participants per week. Over six weeks, this would be 120 participants we anticipate recruiting. If recruitment is higher than anticipated, it will be limited to a maximum of 200 across both sites.

### Statistical Analysis

Data will be analyzed on an intention-to-treat (ITT) analysis basis as well as per protocol analysis (excluding women who requested to stop the program or were lost to follow-up). Data will be analyzed using SPSS (version 29, IBM SPSS Statistics, IBM Corporation). Demographic characteristics will be expressed in means, SDs, and percentages, as applicable, based on group allocation. Any significant differences in baseline characteristics, examined through a chi-square analysis or Mann-Whitney test, will be adjusted for in the analyses. A *P* value of .05 will be considered significant for all outcomes. For all analyses, unadjusted and adjusted models will be reported.

For the effectiveness outcomes, total and summative scores will be reported using means, SDs, and percentages, as appropriate. Analysis of covariance will be used to measure whether scores differ between the two groups, adjusted for the pretest scores and any significant baseline characteristics. For newborn care knowledge, newborn morbidity, newborn mortality, and attendance at postnatal care six-week contact, binary variables will be created, and data will be analyzed using logistic regression.

For the implementation outcomes, descriptive statistics will be used to describe mothers’ experience with ECEM-TZ and outcomes will be reported using means, SDs, and percentages, as applicable. Open-ended questions will be analyzed using thematic analysis [35]. Responses will be transcribed verbatim and translated into English for analysis.

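### Baseline significance tests, rather than prognostic value, decide which covariates beyond the pretest score enter the adjusted models; the logistic models fix no covariate and site is in none

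*Protocol article*

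**What the plan says.** All of this is in the protocol article.

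- **Selection rule** (Statistical Analysis): "Any significant differences in baseline characteristics, examined through a chi-square analysis or Mann-Whitney test, will be adjusted for in the analyses".
- **Score outcomes** (same section): the analysis of covariance is "adjusted for the pretest scores and any significant baseline characteristics". The first half of that phrase is fixed in advance. The second half depends on the data.
- **Binary outcomes** (same section): for knowledge, morbidity, mortality and attendance at the six-week contact, "binary variables will be created, and data will be analyzed using logistic regression". No covariate is named for these models.
- **Reporting** (same section): "For all analyses, unadjusted and adjusted models will be reported". Neither is named as the main one.
- **Significance level** (same section): "A *P* value of .05 will be considered significant for all outcomes". No separate level is given for the baseline tests.
- **Design** (Randomization, Allocation, and Blinding): individual 1:1 computer-generated blocks, and "Stratification based on the site of recruitment will be implemented". Site then appears in no model.
- **Baseline data** (Outcome Measures, Table 1): knowledge, parenting self-efficacy, breastfeeding self-efficacy, anxiety and depression are all measured at T1. Morbidity, mortality and clinic attendance are not.

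**The concern.** In a randomised comparison a baseline test assesses a null hypothesis that the randomisation has already made true. What a covariate adds to the treatment estimate depends on how well it predicts the outcome, and a between-arm P value is silent on that. The rule can admit an irrelevant variable that happens to differ and leave out a strong predictor that happens to be balanced.

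Two things are at stake. One is precision: a given prognostic variable enters only when it is imbalanced by luck. The other is prespecification: the content of the adjusted model is unknown until the data have been split by arm. In logistic regression there is a further effect. Adding a prognostic covariate changes the odds ratio being estimated, so chance also has a hand in which odds ratio is reported.

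**Working it through.** **1. The plan's own figure.** Inputs from Sample Size: 90% vs 70%, 80% power, two-sided 0.05, 1:1. With pooled variance and no continuity correction:

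n per arm = [1.96·√(2·0.8·0.2) + 0.8416·√(0.9·0.1 + 0.7·0.3)]² / 0.2² = (1.109 + 0.461)² / 0.04 ≈ 61.6, so 62 per arm and 124 in total.

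This matches the stated 124. The calculation is for an unadjusted comparison, so the covariate rule does not touch it. Power is 0.803 at 62 per arm, and 0.856 at the 71 and 72 recruited if all are analysed.

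**2. How often chance puts something in.** The number of characteristics tested, k, is not stated, and a level of 0.05 for the baseline tests is assumed. For independent characteristics, P(at least one enters) = 1 − 0.95^k:

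| k (assumed) | P(at least one enters) |
|---|---|
| 5 | 23% |
| 10 | 40% |
| 15 | 54% |
| 20 | 64% |

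Conversely, a given prognostic variable enters in only about 5% of trials.

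**3. A lone prognostic covariate, nothing else fixed.** Simulated linear model, 71 vs 72, 20,000 runs per setting, standardised effect 0.47 (about 80% unadjusted power). The correlations with the outcome are assumptions.

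| Correlation | Power, selection rule | Power, prespecified | Type I error, selection rule |
|---|---|---|---|
| 0.3 | 0.80 | 0.83 | 0.048 |
| 0.5 | 0.81 | 0.90 | 0.044 |
| 0.7 | 0.81 | 0.97 | 0.036 |

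At correlation 0.5 the standard error of the effect is 0.166 unadjusted, 0.160 under the rule and 0.144 prespecified. This is the upper bound of the problem. It does not describe the planned analysis of covariance, which already contains the pretest.

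**4. Score outcomes as planned.** Pretest always in the model (assumed r = 0.5), one further covariate selected at P<.05, 62 per arm, effect 0.507, 6,000 runs.

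| Incremental R² (assumed) | Power, selection rule | Power, always adjusted | Loss (points) |
|---|---|---|---|
| 0.02 | 89.6% | 89.7% | 0.1 |
| 0.05 | 88.8% | 90.3% | 1.5 |
| 0.10 | 90.6% | 93.4% | 2.8 |

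The pretest alone lifts power from about 80% to about 90%. The rule puts only the remainder at risk.

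**5. Binary outcomes as planned.** Logistic model, marginal proportions 70% vs 90%, no fixed covariate: the loss against a prespecified strong covariate is about 3 to 7 points. A check at 71 vs 72 (likelihood-ratio tests, 5,000 runs, one standard normal covariate) shows how this depends on the assumed strength. With a log odds ratio of 0.5 per SD the loss is under 1 point. At 1.0 it is 3.0 points (88.7% vs 91.8%, before rounding) and at 1.5 it is 5.8 points (88.4% vs 94.1%, before rounding). At an extreme 2.0 it reaches about 8.

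**6. Rare outcomes.** The Introduction gives neonatal mortality of 20 per 1000. For 143 mothers that is 143 × 0.020 ≈ 3 deaths, and probably fewer, because newborns who die before discharge are excluded. A logistic model for mortality cannot support covariates that enter by chance.

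**The case against.** The best defence is that the plan already does much of what is wanted. The pretest score, usually the strongest single predictor, is fixed for all five score outcomes. Unadjusted models are reported alongside and do not depend on the rule. The trial was sized on an unadjusted comparison, so no promised power is lost. An irrelevant covariate in a linear model with 124 or more participants costs very little. All of this stands, and it is why the loss for the scores is only about 0 to 3 points.

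It does not reach the logistic models, where no covariate is fixed, or site, which is fixed nowhere. Nor does reporting both models settle which one answers the question for each outcome.

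Three stronger readings are tempting, and the article supports none of them:

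- **Inflated false positives.** A reader might infer that a two-stage procedure breaks the 5% level upwards. In the lone-covariate simulations it falls slightly below: 3.6% to 4.8%.
- **Covariates picked to suit the result.** The article does say "The researchers will be aware of participant allocation", but it also keeps those researchers out of data collection and randomisation. The rule is mechanical, with named tests applied to baseline characteristics and not to outcomes. What remains is that the model is fixed only after the data are split by arm.
- **Most of the available precision is thrown away.** That holds only for a lone covariate with nothing else in the model, which is not the planned analysis of the scores.

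**Conclusion.** The point holds in a limited form. The article states a rule, rather than leaving a detail to an analysis plan, and the rule lets chance imbalance choose every covariate beyond the pretest score. The cost is some lost precision and an adjusted model that is not fixed in advance. Neither bias nor extra false positives has been shown.

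The score outcomes are affected little. The logistic models are affected more, above all binary knowledge, where a T1 measurement exists and is not used. These sizes rest on assumed covariate strengths, since the article gives none, and weak covariates would make the loss negligible. The sample size of 124 and its 80% power stand. This is a free improvement, not a flaw that threatens the trial's conclusions.

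**What to change.** In Statistical Analysis:

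1. Delete the sentence that selects covariates by baseline testing, and the reference to significant baseline characteristics in the sentence on analysis of covariance.
2. State that each adjusted model contains arm, recruitment site and the T1 value of the outcome where measured, including in the logistic model for knowledge.
3. Allow at most a short list of further prognostic variables, fixed before the data are viewed by arm. Keep covariates to a minimum for rare outcomes such as newborn mortality.
4. Name which of the unadjusted and adjusted models is the main one.
5. Present baseline characteristics descriptively, without P values.

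The cost is wording only. Site and the T1 scores are already collected, the sample size does not change, and the note to the flow diagram says the analysis was not yet complete. If the data have since been viewed by arm, the change should be dated and reported as made after that point.
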